### Intervention

2.3

In order to test this new tool as a patient monitoring instrument, the study will investigate the responsiveness of the new panel of markers associated with FM in the assessment and monitoring of treatment. The treatment group will undergo a nutritional intervention based on the Mediterranean diet using EVOO as a supplement, and the placebo group will receive OO. Both groups will be under nutritional control, with regular follow-up calls (twice a month) by their assigned nutritionist. Dietary adherence will be monitored by 24 h dietary recall, as well as a deeper nutritional interview. To avoid excessive withdraw, nutritionist will provided a wide repertoire of foods and cooking tips. The participants will receive a semi-customized list of three-week menus to exchange throughout the intervention (Supplementary material S2). Additionally, they will consume 50 ml of the assigned raw oil, freely distributed through the main meals during the day. This treatment regimen will be administered over a period of 6 months. Figure 2 illustrates the design of the nutritional intervention that will be followed.

**Figure 2 fig2:**
[figure not shown]
Graphic of the nutritional intervention design and collection kit.

### Data collection and procedures

2.4

#### Health questionnaires

2.4.1

Participants will complete the Spanish version of the SF-36 health questionnaire following the methodology described by Vilagut et al. (31) in every sample collection, for a total of four data points. This questionnaire aims to assess the participants’ physical and psychological well-being. It consists of 36 questions, referred to therein as items, and covers eight specific scales: physical functioning (PF), role limitations due to physical health (PH), bodily pain (BP), general health perceptions (GH), vitality (V), social functioning (SF), role limitations due to emotional problems (EP) and mental health (MH). Additionally, it includes an item that evaluates participants’ overall health compared to the preceding year. A higher score indicates a better health status. FM patients will complete the fibromyalgia impact questionnaire (FIQ) to assess FM impact on their daily lives. This questionnaire evaluates various aspects, including physical functioning, work performance (missed workdays and work difficulty), depression, anxiety, morning fatigue, pain, stiffness, fatigue and overall well-being during the preceding week. The FIQ consists of 21 items divided into three main domains: function (*n* = 9), overall impact (*n* = 2) and symptoms (*n* = 10). Each item is scored on a scale of zero (no impairment) to 10 (maximum impairment), and the total function score is divided by three. The sum of the scores for overall impact remains unchanged, while the sum of the scores for symptoms is divided by two. The total score of the questionnaire is then calculated by adding these three scores, with the maximum possible total score being 100.(1)
$$FIQ=\frac{\Sigma \mathrm{Function}}{3}+\Sigma \mathrm{Overall Impact}+\frac{\Sigma \mathrm{Symptons}}{2}$$

Questionnaire’s data will be analyzed to search for mean differences. This analysis will help us to strengthen and demonstrate how FM syndrome impact in the quality of life of the patients. Besides, the scores will be used to analyze potential correlations between them and the biomarkers found.

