
#### Statistical analysis

2.4.6

The statistical analysis will be performed in RStudio, using R v3.6.2 base packages. First, data distribution will be assessed by using the Kolmogorov–Smirnov test, which evaluates the null hypothesis that data correspond to normal distribution. In that case, in analyses of CONTROL vs. FM groups T_0_, parametric tests such as the unpaired student’s *t*-test and the Pearson correlation test will be used to investigate mean differences and correlation between quantitative variables, respectively. If data do not display normal distribution, the Mann–Whitney *U* test and the Spearman correlation non-parametric test will be applied for this purpose. Additionally, for comparison among groups when depicting nutritional intervention influence with treatment vs. placebo, pre-post analysis through analysis of covariance (ANCOVA) with multiple comparison correction will be used, since it has been shown to be the most powerful analysis for this experimental design (39). In all cases, the significance level (*α*) will be established at 0.05 so that null-hypothesis will be rejected when the *p*-value is <0.05. Tables will be used as preferred format to show descriptive data, such as demographic characteristics, stacked bar charts and/or pie charts will be used to represent distributions, bar charts and/or box and whiskers plots will be applied when showing differences in mean among groups and, finally, violin plots, volcano plots and additional statistical representations will be the format to show distribution and significance in the values found in each group.

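### Section 2.4.6 places unadjusted correlations inside the CONTROL vs FM analysis; if the groups are pooled, SF-36 and the selected biomarkers correlate in expectation with no association within either group

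*Protocol article*

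**What the plan says.** - **Use of the scores.** Section 2.4.1 (Health questionnaires) ends by saying that "the scores will be used to analyze potential correlations between them and the biomarkers found". It does not say whether this means FM patients, controls or both.
- **Who answers what.** SF-36 is for everyone: "Participants will complete the Spanish version of the SF-36 health questionnaire". FIQ is restricted: "FM patients will complete the fibromyalgia impact questionnaire (FIQ").
- **Expected SF-36 difference.** The mean comparison of the questionnaires is meant to "demonstrate how FM syndrome impact in the quality of life of the patients", so a group difference is expected. Its size is not given.
- **Test and setting.** Section 2.4.6 (Statistical analysis) introduces the correlation tests "in analyses of CONTROL vs. FM groups" at T0. For normal data, the unpaired t-test and "the Pearson correlation test will be used to investigate mean differences and correlation between quantitative variables". Otherwise the Mann–Whitney test is used and "the Spearman correlation non-parametric test will be applied for this purpose". No within-group analysis and no adjustment for group is mentioned.
- **Which biomarkers.** The closing summary of the Discussion describes the aim as a signature that separates FM patients from healthy controls.

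**The concern.** Both variables in the planned correlation are tied to diagnosis: the marker because it is selected for a group difference, SF-36 because FM is expected to lower it. If one coefficient is computed over both groups, diagnosis acts as a common cause. The two clouds of points sit at different means, and the line joining the means produces a correlation whether or not the marker follows the score among women of the same group.

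Such a coefficient can be taken to show that a marker tracks symptom burden when it only repeats the case-control difference. It can also seem to corroborate a marker that passed selection by chance, because the chance difference in the marker is carried into its correlation with SF-36.

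**Working it through.** **The plan's own figure.** The plan gives none for this point. Its minimum of 206 participants comes from a prevalence-precision formula with no group difference or correlation in it: 1.96² × 0.075 × 0.925 / 0.0375² = 189.5, and × 1.1 = 208.5 (207.0 with the unrounded mean prevalence of 7.55%). That is close to 206 but has no bearing here.

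**Inputs from the document.** 250 participants (section 2.2.2); equal numbers of patients and controls, from blocks of 4 and 4 (section 2.1), so about 125 per group; α = 0.05 (section 2.4.6), taken as two-sided.

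**Assumptions.** Normal data, equal within-group variances and zero correlation within each group. The group difference is a = 0.3, 0.5 or 0.8 SD in the marker and b = 1, 1.5 or 2 SD in SF-36. The document gives neither a nor b, so a range is shown.

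**Formula.** With two equal groups, the between-group part adds ab/4 to the covariance, a²/4 to the marker variance and b²/4 to the SF-36 variance. In size,

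|r| = (ab/4) / √[(1 + a²/4)(1 + b²/4)].

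The sign follows the direction of the two differences. Two worked cases:

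- a = 0.3, b = 1: 0.075 / √(1.0225 × 1.25) = 0.066.
- a = 0.8, b = 2: 0.40 / √(1.16 × 2) = 0.263.

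The chance of p<0.05 follows from Fisher's z, with mean atanh(r) × √(250 − 3). For r = 0.066 the mean is 1.04, giving 18%. For r = 0.263 it is 4.23, giving 99%.

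| SF-36 difference | Marker 0.3 SD | Marker 0.5 SD | Marker 0.8 SD |
|---|---|---|---|
| 1.0 SD | 0.07; 18% | 0.11; 40% | 0.17; 75% |
| 1.5 SD | 0.09; 29% | 0.15; 63% | 0.22; 95% |
| 2.0 SD | 0.11; 38% | 0.17; 78% | 0.26; 99% |

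(Each cell: |r|; chance of p<0.05 at N = 250. At N = 206 the chances run from 16% to 97%.)

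**Check by simulation** (6,000 trials per cell, N = 250, keeping only markers with t-test p<0.05):

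- Selection raises the rates most for weak markers. At 0.3 SD they become 24%, 40% and 55% for SF-36 differences of 1, 1.5 and 2 SD.
- Markers with no true group difference that pass selection by chance are significant against SF-36 in about 17% to 33% of pooled tests.
- In the same selected trials, the test within FM alone, or adjusted for group, is significant in about 4% to 6.5%, in line with the nominal 5%.

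These figures are for Pearson. The mechanism is the same for Spearman, but that was not computed.

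**Power of the alternative**, for a true within-group r of 0.25 (atanh = 0.2554):

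- Within 125 FM women: 0.2554 × √122 = 2.82; 2.82 − 1.96 = 0.86; power about 81%.
- Group-adjusted over 250: 0.2554 × √246 = 4.01; 4.01 − 1.96 = 2.05; power about 98%.

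**The case against.** The strongest reply is that the document never says the groups are pooled. The phrase "in analyses of CONTROL vs. FM groups T_0" may only separate the baseline stage from the later treatment-versus-placebo ANCOVA, and separate correlations in each group would fit the text. The article is condensed, and the population for a supportive correlation could be left to the analysis plan. The first part stands: pooling is a reading, though the natural one, since the two-group comparison is the only setting given. The second does not remove the point. The article does fix a test and a setting, and applying that unadjusted test to that setting gives the confounded result.

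Other parts of the reply limit what can be claimed. A reader might infer any of the following, and the document does not support them:

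- **That selected markers are bound to correlate significantly with SF-36.** Only the expected coefficient is non-zero, and only under pooling. Significance depends on differences that the document does not state.
- **That a pooled coefficient carries no information on severity.** With a common within-group correlation ρ, the numerator becomes ρ + ab/4. Real association is in it, mixed with the group effect, and an opposing ρ could cancel that effect.
- **That the plan rests its monitoring claim on these correlations.** Section 2.3 ties monitoring to the panel's responsiveness under the intervention.
- **That the FIQ correlations share the problem.** They do not: only FM patients complete FIQ, so those correlations are within patients by design.

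**Conclusion.** The point holds in conditional form. Section 2.4.6 puts unadjusted correlation inside the two-group baseline analysis, and section 2.4.1 does not restrict the population. If SF-36 is correlated with the selected markers over both groups, no within-group association is needed for a correlation to appear. The false-positive rate for a within-group link is about 18% to 99% at 125 per group, against 5%, across the assumed differences. The width of that range reflects how little the document says about effect sizes; even its lower end is more than three times nominal. The point concerns a supportive SF-36 analysis. It touches neither the case-control comparison itself, nor the ANCOVA of the intervention, nor FIQ. It is worth correcting because the misreading is easy and the remedy nearly free.

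**What to change.** Add to section 2.4.6 that correlations between SF-36 scores and biomarkers are computed within FM and within CONTROL separately, or as a partial correlation adjusted for group, and that an unadjusted coefficient over both groups is not reported as evidence that a marker tracks symptom burden. Nothing needs to change for FIQ.

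The cost is one sentence, with no change to sample, visits or assays. The price of the within-FM analysis is that it uses about 125 women instead of 250. Where the association can be taken as similar in both groups, the group-adjusted version recovers most of that loss.

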#### Plasma proteome analysis

2.4.2

Whole blood samples from participants will be collected through venipuncture performed by a healthcare professional. The samples will be collected in two tubes containing heparin-lithium as an anticoagulant. Moreover, to minimize circadian fluctuations of the markers, the blood samples will be taken at the same time of day and participants will have fasted beforehand. While one of the tubes will be used for oxidative stress and mitochondrial metabolism analysis, the other one will be transferred to a 15 ml Falcon tube and then centrifuged at 2,300 RCF for 10 min at 4°C. This process will isolate the plasma, the sample to be used in the proteome analysis that will be aliquoted and stored at −80°C until batch analysis (maximum storing: 5 months). To analyze the plasma proteome, liquid nano-chromatography coupled to the tandem mass spectrometry (nLC-MS/MS) proteomic method will be applied. This analysis will utilize the EvoSEP chromatograph,^1^ which is one of the highest resolution and processing chromatographs available. It is a unique instrument in Spain and is accessible through the services of the BioGUNE Cooperative Research Center in Biosciences located in Biscay, Spain. The processed data will be analyzed with the search engines MASCOT (MatrixScience) and/or PEAKS (Bioinformatics Solutions Inc). Label-free quantification differential proteomics will be performed using PEAKS (Bioinformatics Solutions Inc) and/or MaxQuant software. Quality control of samples will be applied at each step through protein-suitable techniques such as Bradford quantification, electrophoresis and/or Ponceau staining.

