### Study design

2.1

This is a randomized, prospective, low-interventional, double-blinded and placebo-controlled clinical trial. This study will be performed on adult women who meet ACR diagnostic criteria for FM (FM group), along with age-matched healthy volunteers (CONTROL group). The double-blinded, placebo-controlled, randomized experiment will be conducted by using extra virgin olive oil (EVOO) as treatment and olive oil (OO) as placebo, being under nutritional intervention in adherence to a Mediterranean diet supplemented with one of the olive oils for 6 months since the first sample collection. The participants will be assigned to each group randomly, using the balanced block randomization method. Briefly, once participants have been chosen for project enrollment, they will be tagged with an ordinal numeric code with three numbers by an employee from the company not related with the project nor the laboratory. This same employee will decide the codification of treatment (EVOO) and placebo (OO) groups, by assigning them an “A” or a “B” letter. Then, a second employee neither related with project or lab workflow, will randomly allocate these codes to 8-individuals blocks composed by 4 patients and 4 healthy volunteers. These blocks will be assigned to a treatment group by following the pattern ABBAABBA. In this process, this second employee will only have access to the date and time in which the participation form was completed as a unique identifier, as well as the condition of the participant: patient (FM) or healthy volunteer (CONTROL). This process will ensure that no one can link any code to its health condition, neither to participants’ data. Both processes will be reflected in patients’ database and documented in a password encrypted word file that will be also kept physically in a key-protected drawer during the entire project. The blinding method will be maintained until the data have been fully analyzed, and once this information is required to write the scientific communications that will be generated. As a result, both, patients and researchers will be fully blinded about treatment to be taken and health conditions from each participant code. Furthermore, by following the balanced block randomization method, the treatment and placebo group will comprise the same number of patients and healthy individuals. The study will span a total duration of 12 months, during which four blood and stool samples will be collected from each participant: the first before nutritional intervention (T_0_), the second after 3 months of nutritional intervention (T_1_), the third at the conclusion of the six-month nutritional intervention (T_2_) and the fourth 6 months after the end of the intervention (T_F_). This final timepoint have been included to check whether the identified biomarkers that response to nutritional intervention would change back again to the baseline, indicating a strong dependance between nutritional habits and these specific biomarkers. Figure 1 illustrates the workflow that will be followed in this study.

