#### Microbiota and intestinal permeability analysis

2.4.5

Participants will collect fecal samples using the DANASTOOL sample collection kit (Danagen; Barcelona, Spain). They will use a Fe-Col^®^ Faecal sample collection paper (Alpha Laboratories; Hampshire, United Kingdom) as a stool-catch platform. The participants will scoop a small portion of stool into the provided stool tube, which contains a liquid DNA/RNA stabilization solution. Following collection, all samples will be stored in accordance with established quality standards. Since the DANASTOOL sample collection kit has a DNA/RNA stabilization solution, samples were stored at room temperature until batch analysis. DNA extraction from fecal samples will be carried out using the DANAGENE MICROBIOME FECAL DNA KIT (Danagen; Barcelona, Spain). Briefly, 1 ml of homogenized sample was transferred to a tube containing beads to ease sample disruption. Then, samples were incubated at 70°C during 10 min. After incubation step, a thorough vortexing and centrifugation steps were applied. The upper phase was then transferred to a filtering column to extract DNA by centrifugation. The extracted DNA will then be used to analyze the composition of the gut microbiota. This analysis will involve amplicon metagenomics sequencing, in which amplicons of V3–V4 regions from the 16S rDNA will be sequenced using the Illumina MiSeq platform at HelixBioS (Madrid, Spain) facilities. A tagging and barcoding process suitable for Illumina technology will be conducted, according to manufacturer instruction. Each sample will undergo individual quantification, pooling, washing and titration using qPCR. The sequencing will be performed on the MiSeq platform with a fragment size ranging from 2 × 250 to 2 × 300, with the aim of generating 150,000 to 200,000 reads per sample. We will set the minimal number of reads per sample at 50,000 as quantity threshold, and Phred Score at Q30 as quality threshold. Samples with an average trimmed read length below 280 bp will be discarded. All these quality control procedures will be applied through MultiQC software (36) and sequencing results will be analyzed with USEARCH V11.1. Briefly, the reads will be cleaned using the UCHIME algorithm to eliminate “singletons” sequences (those that only had one copy in the total sequences), chimera sequences and possible artifacts. ZOTUs clustering will be carried out using the UNOISE algorithm at 99% identity (similarity). The sequences will be then aligned against the taxonomic database developed for the study of the intestinal microbiota, HUMAN GUT 16S (HelixBioS), with an alignment cut-off point of 99% (identity) using the algorithm USE-LOCAL. The results will be finally processed with phyloseq (37) and DESeq2 (38).

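### The T0 FM versus CONTROL comparison names a test without a batch term, and nothing stated carries the 4+4 block balance into the assay runs

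*Protocol article*

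**What the plan says.** All references are to the protocol article.

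- **Plasma (2.4.2):** aliquots are frozen "until batch analysis (maximum storing: 5 months").
- **Stool (2.4.5):** "samples were stored at room temperature until batch analysis", with no time limit given. The extracted DNA is tagged, pooled and sequenced, and the results are processed with phyloseq and DESeq2.
- **Mitochondrial proteins (2.4.4):** VDAC and MAP1LC3B are measured by western blot after gel electrophoresis, with vinculin as loading control.
- **Blinding (2.1):** "patients and researchers will be fully blinded about treatment to be taken and health conditions from each participant code".
- **Blocks (2.1):** codes go into "8-individuals blocks composed by 4 patients and 4 healthy volunteers". "These blocks will be assigned to a treatment group by following the pattern ABBAABBA". No other use of the blocks is described. The second employee, who is outside the project and the laboratory, forms them and sees the form's time stamp "as well as the condition of the participant: patient (FM) or healthy volunteer (CONTROL").
- **T0 analysis (2.4.6):** the sentence begins "in analyses of CONTROL vs. FM groups T_0_, parametric tests such as the unpaired" t-test, with Mann-Whitney U if normality fails. A covariate model (ANCOVA) is named only for the oil comparison.

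**The concern.** The FM versus CONTROL contrast at T0 serves the primary aim, a diagnostic panel. Measurements made in separate LC-MS sequences, gels or sequencing pools can differ by run for reasons unrelated to disease. If one run holds more FM samples than another, a run difference appears as an FM difference, and it can do so across many features at once. A correction for multiple comparisons does not remove such a bias.

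The laboratory cannot even out the runs itself because it does not know who has FM. The structure that would do so, the 4+4 block, stops at oil allocation. The named two-sample test cannot repair an imbalance afterwards. Recruitment runs through FM associations and social media (2.2.2), and these channels could deliver patients and healthy women at different rates.

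**Working it through.** **Plan's own figure.** There is none on this point: no batch number, batch size or batch variance. The stated minimum of 206 participants comes from a prevalence-precision formula and has no bearing on batch effects.

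**Inputs.** From the article: 250 women, 4+4 blocks, alpha 0.05. Assumed: 125 FM and 125 CONTROL, a two-sided test, 4 equal batches, within-batch SD 1, batch SD (σ) 0.3 or 0.5, and the FM shares shown below.

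**Formula.** Let p_k be the fraction of the FM group in batch k, and w_k that fraction minus the CONTROL fraction.
- True variance of the mean difference: 2/125 + σ²·Σw_k².
- Variance the t-test assumes: (2/125)·[1 + σ²·(1 − Σp_k²)].
- Null rejection: 2·[1 − Φ(1.96·SE_test/SD_true)].

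**Worked case, FM shares 65/55/45/35%.** p = 0.325, 0.275, 0.225, 0.175 and w = 0.15, 0.05, −0.05, −0.15, so Σw² = 0.05 and Σp² = 0.2625.
- σ = 0.5: SD_true = √(0.016 + 0.0125) = 0.169; SE_test = √(0.016 × 1.184) = 0.138; ratio 1.60; rejection about 11%.
- σ = 0.3: SD_true = √(0.016 + 0.0045) = 0.143; SE_test = √(0.016 × 1.066) = 0.131; ratio 1.79; rejection about 7.4%.

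| FM share per batch (%) | σ | Null rejection, formula | Null rejection, simulation (6,000 runs) |
|---|---|---|---|
| 65/55/45/35 | 0.3 | 7.4% | 7.8% |
| 65/55/45/35 | 0.5 | 11.0% | 10.2% |
| 60/53/47/40 | 0.3 | 5.6% | 5.7% |
| 60/53/47/40 | 0.5 | 6.5% | 6.6% |
| 50 throughout | 0.3 | 4.3% | 4.3% |
| 50 throughout | 0.5 | 3.3% | 3.1% |

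A further 20,000 runs per cell gave, in the same order, 7.2%, 10.0%, 5.5%, 5.9%, 4.6% and 3.5%.

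**With a batch term.** At 65/55/45/35% the 6,000-run simulation gives null rejection of 5.2% and 4.8%. Power at d = 0.4 is 86.5% and 86.6%, against 84.5% and 77.6% unadjusted. With equal shares, power is 88.2% and 88.5% with the term, against 86.6% and 84.2% without it, a loss of 1.6 and 4.3 points.

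**One marker with a fixed shift.** Take two equal batches, a shift s between them, and a fraction q of FM women (1 − q of CONTROL) in batch 1. The false difference is s·(2q − 1). At s = 0.5 and q = 0.7 this is 0.20 SD. The test's SE is √(0.016 × 1.0525) = 0.130, so rejection is about 1 − Φ((1.96 × 0.130 − 0.20)/0.1265) = 33%. At q = 0.6 it is 11%.

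**Why layout matters as well as the model term.** In the two-batch case, adjustment multiplies the variance of the FM effect by 1/[1 − (2q − 1)²]: 1.04 at 60/40, 1.19 at 70/30 and 1.56 at 80/20. Power at d = 0.4 falls from 88.5% at balance to 87.3%, 82.6% and 71.6%. Balance within runs avoids this loss.

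**When the harm vanishes.** If batch membership is unrelated to FM status, the unadjusted test holds its level: 4.8% to 5.3% for shifts of 0.5 to 2.0 SD. If samples simply follow block order, the running FM-minus-CONTROL count never exceeds 4. A batch of 62 can then differ by at most 8 (35 versus 27, about 56/44), and simulated rejection stays at about 5%.

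**The case against.** A reader might infer that T0 samples will be run in calendar batches with FM and CONTROL unevenly spread, so that false biomarkers are built in. The article does not support that. It gives a 5-month cap for plasma, no cap for stool, and no recruitment window, batch number or run order. If T0 collection finishes within 5 months, a single plasma campaign is possible; only a longer collection forces at least two. Whole 4+4 blocks may also enter together, which would keep runs close to balance.

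A reader might also infer that blinding rules out balanced runs. It does not: an employee outside the laboratory knows each woman's status.

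Other parts of the objection also stand. Batch layout is often left to a laboratory procedure or analysis plan, so silence here does not prove absence. The T0 tests are introduced as examples. DESeq2 can take a batch factor, although none is named. Vinculin addresses loading, although it is not presented as a correction between gels. Total antioxidant capacity is read on strips and is not described as batched.

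What remains is that the article does name a T0 method, that method has no place for batch, and the one balancing device it describes is given no role in the assays.

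**Conclusion.** The point holds as a cheap improvement to the T0 FM versus CONTROL analysis, not as proof of bias. Under the assumed batch SDs, the false-positive excess is 2 to 5 percentage points at 65/55/45/35% and about 1 point at 60/53/47/40%. It is absent when runs are balanced or follow block order. Even at balance, the unadjusted test is conservative and gives up about 1 to 5 points of power at d = 0.4. A single marker with a large fixed shift and strong imbalance would fare much worse. The batch number, batch SD, imbalance and 125/125 split are all assumptions. The oil comparison, comparisons between visits and the strip-based antioxidant readings are outside this point.

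**What to change.** 1. **Run list.** The outside employee who forms the blocks gives the laboratory a coded list. Each block's 4 FM and 4 CONTROL T0 samples stay in the same LC-MS sequence, gel and sequencing pool, in random order within the run. The list shows codes, run and position only, so blinding to status is kept.
2. **Analysis.** Replace the unadjusted T0 two-sample test with a linear model for FM status with batch as a term, or a rank test stratified by batch when a rank method is needed. For stool, include batch in the DESeq2 design.
3. **Text.** State in 2.4.2, 2.4.4 and 2.4.5 how samples are assigned to runs, and in 2.4.6 that batch is in the T0 model.

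The cost is one list and one model term, with no additional samples or assays. The downside is that a sample may have to wait for its block partners, within the 5-month plasma limit. The list has to be in place before the T0 runs, because a poor layout can be only partly repaired by adjustment afterwards.
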